## 11.4.2 Secondary Efficacy Analysis

### 11.4.2.1 Key Secondary Efficacy Analysis

The same analysis as the primary efficacy analysis will be performed for the PPS for Immunogenicity. The same supplementary analyses will also be performed for the FAS for Immunogenicity.

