In Study DS5670-146, the blood neutralizing activity against SARS-CoV-2 increased at 4 weeks after study drug administration. Therefore, the time point of 4 weeks after study drug administration was selected as the time to evaluate the primary endpoint, considering the time point of safety evaluation for subjects (at 4 weeks after study drug administration) and the convenience for subjects to visit.

In accordance with the "Principles for the Evaluation of Vaccines Against the Novel Coronavirus SARS-CoV-2," a solicited AE observation period of 7 days and an AE observation period of 28 days after administration of DS-5670d were included to collect information on specific injection site reactions and specific systemic reactions occurring for at least 7 days and safety events occurring for at least 28 days after SARS-CoV-2 vaccine administration. In addition, a follow-up period of 52 weeks after study drug administration was included to collect information on long-term efficacy and safety including antibody dependent enhancement (ADE) after SARS-CoV-2 vaccine administration.

In Japan as in other countries, if the majority of the population have acquired basic immunity due to vaccination with SARS-CoV-2 vaccine or SARS-CoV-2 infection, the policy is likely to be changed to a single dose regardless of the history of SARS-CoV-2 vaccination or SARS-CoV-2 infection. Therefore, a study to obtain the indication of this vaccine as a single dose was to be conducted. In the primary analysis, the non-inferiority of DS-5670d to Comirnaty RTU IM will be verified in adults and children aged 12 years and older with at least either a history of SARS-CoV-2 infection or vaccination with SARS-CoV-2 vaccine in whom a single dose is expected to induce sufficient immunity. In the secondary analysis, the non-inferiority of DS-5670d to Comirnaty RTU IM will be verified in all populations including those without a history of SARS-CoV-2 infection or a history of SARS-CoV-2 vaccination, assuming a society where the vaccine will be administered to some individuals without basic immunity.

After issuance of the notification from the Pharmaceutical Evaluation Division dated March 4,

Confidential

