#### 5.1.2 Method of Treatment Allocation

The independent biostatistician will prepare a subject randomization list showing a correspondence between subject numbers and study drugs (investigational product or comparator).

Subjects will be randomized in a 1:1 ratio to the DS-5670d group or Comirnaty RTU IM group, with study site, age (12 to 17 years, 18 to 64 years, 65 years and older), the presence or absence of a history of SARS-CoV-2 infection (yes, no), the presence or absence of a history of vaccination with SARS-CoV-2 vaccine (yes, no) as stratification factors based on the information entered in the Interactive Response Technology (IRT). The presence or absence of a history of SARS-CoV-2 infection used as a stratification factor will be based on the history of SARS-CoV-2 infection reported by the subject or legal representative at informed consent (self-reported SARS-CoV-2 infection history) and the SARS-CoV-2 antibody test result from the rapid test kit at the time of eligibility evaluation. A subject will be defined as having a history of SARS-CoV-2 infection if he/she is determined to have a self-reported SARS-CoV-2 infection history at informed consent or have a positive SARS-CoV-2 antibody with the rapid test kit at the time of eligibility evaluation. Otherwise, the subject will be defined as having no history of SARS-CoV-2 infection.

The procedures for subject enrollment are shown in [Figure 5.1-1](#).

After obtaining written consent from the subject or subject's legal representative, the investigator or subinvestigator will prepare a subject screening list, and confirm the eligibility of the subject.

The investigator, subinvestigator, or study staff will register the required information in the IRT after obtaining informed consent. The IRT will allocate a study-specific subject number. The investigator, subinvestigator, or study staff will enter confirmation of the subject eligibility in the IRT. The IRT will randomize the eligible subject to an administration and notification of the assigned study drug will be sent to the unblinded personnel at the study site (See Section 5.1.3).

After the unblinded personnel at the study site (study drug manager or study drug management assistant designated by the study drug manager, study drug preparer, and study drug administration personnel) will confirm the assigned study drug based on the IRT notification, the assigned study

Confidential

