Multiplicity of the test associated with multiple non-inferiority hypotheses in multiple populations (ABC combined and ABCD combined) will be controlled by fixed sequence testing. First, the non-

Confidential

inferiority of the DS-5670 group to the Comirnaty RTU IM group will be tested in the ABC combined population, and only if the non-inferiority is confirmed, the non-inferiority of the DS-5670d group to the Comirnaty RTU IM group will be verified in the ABCD combined population. All hypotheses will be evaluated at a one-sided 2.5% significance level.

With reference to the PMDA notification "Principles for the Evaluation of Vaccines Against the Novel Coronavirus SARS-CoV-2, (Appendix 4) Immunogenicity-based evaluation of variant vaccines modified from parent vaccines and booster vaccines with new active ingredients," the non-inferiority margins for the GMT ratio and the difference in the seroresponse rate are set at 0.67 and -10%, respectively.

In this study, analyses will be performed twice. The first analysis will be the primary analysis of immunogenicity and safety. The primary immunogenicity and safety endpoints will be evaluated to verify the non-inferiority of DS-5670d group to Comirnaty RTU IM group once when immunogenicity and safety data are collected for all subjects for 4 weeks after study drug administration or when the study is terminated. The second analyses will be performed when or the immunogenicity and safety data for 26 weeks after study drug administration have been obtained for all subjects or the study termination.

Unless otherwise specified, continuous variables will be summarized by presenting the number of subjects, arithmetic mean, standard deviation, minimum, median, and maximum, and categorical variables will be summarized by calculating the frequency and proportion. Unless otherwise specified, baseline values from each subject will be the last observed values that are available before study drug administration. Changes from baseline (eg, change, shift table) will be analyzed in subjects whose baseline values and at least one post-treatment value are available. An outline of the statistical analyses is provided below. Statistical methods will be specified in more details in separately prepared Statistical Analysis Plan (SAP).

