#### 11.4.1 Primary Efficacy Analysis

The following analyses will be performed for the Immunized PPS for Immunogenicity.

The GMT ratio (DS-5670d group vs. Comirnaty RTU IM group) for blood neutralizing activity against SARS-CoV-2 (Omicron strain XBB.1.5.6) at 4 weeks after study drug administration and its 2-sided 95% confidence interval will be calculated by administration arm. The difference in seroresponse rate (DS-5670d group – Comirnaty RTU IM group) for blood neutralizing activity against SARS-CoV-2 (Omicron strain XBB.1.5.6) at 4 weeks after study drug administration and its 2-sided 95% confidence interval will be calculated.

A linear model will be applied with blood neutralizing activity against SARS-CoV-2 (Omicron strain XBB.1.5.6) at 4 weeks after study drug administration as an explained variable, administration

Confidential

arm as an explanatory variable, and baseline value (common logarithmic value), a history of SARS-CoV-2 infection and vaccination with SARS-CoV-2 vaccine as covariates, based on which the GMT ratio (DS-5670d group vs. Comirnaty RTU IM group) and its 2-sided 95% confidence interval will be calculated. The covariates may be changed depending on subject enrollment.

In addition, the difference in seroresponse rate (DS-5670d group – Comirnaty RTU IM group) for blood neutralizing activity against SARS-CoV-2 (Omicron strain XBB.1.5.6) at 4 weeks after study drug administration and its 2-sided 95% confidence interval will be calculated. This analysis may be changed to stratified analysis depending on subject enrollment.

DS-5670d will be judged to be non-inferior to Comirnaty RTU IM if the lower limit of 2-sided 95% confidence interval in adjusted GMT ratio (DS-5670d group vs. Comirnaty RTU IM group) is greater than 0.67 and simultaneously the lower limit of 2-sided 95% confidence interval of the difference in seroresponse rate (DS-5670d group – Comirnaty RTU IM group) is greater than –10%.

The same supplementary analyses will also be performed for the Immunized FAS for Immunogenicity.

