#### Power for the primary objective

With the sample size of 690 subjects in the population with at least either a history of SARS-CoV-2 infection or vaccination with SARS-CoV-2 vaccine (ABC combined) and an assignment ratio (DS-5670d group : Comirnaty RTU IM group) of 1:1, and assuming that the percentage of enrolled subjects who do not contribute to immunogenicity evaluation due to reasons such as exclusion from analysis set and subjects' withdrawal from the study is 10.0%, the GMT ratio (DS-5670d group vs. Comirnaty RTU IM group) for blood neutralizing activity against SARS-CoV-2 at 4 weeks after study drug administration is 1.0, and the common standard deviation of neutralizing activity (common

Confidential

logarithmic value) is 0.533, the statistical power to detect the non-inferiority for GMT would be 98.2% at 1-sided significance level of 0.025. The standard deviation was determined based on the results of Study DS5670-103 and Study DS5670-146 to compare DS-5670a and Comirnaty IM (monovalent: original strain) in subjects aged 18 years and older.

On the other hand, assuming that the seroresponse rate for blood neutralizing activity against SARS-CoV-2 at 4 weeks after study drug administration is 80.0% in both the DS-5670d group and Comirnaty RTU IM group, the statistical power to detect the non-inferiority for seroresponse rate would be 87.2% at 1-sided significance level of 0.025.

Therefore, the power for the non-inferiority which simultaneously satisfies these primary endpoints is 85.6% ( $= 98.2\% \times 87.2\%$ ) assuming that the non-inferiority in terms of GMT and seroresponse rate are respectively independent.

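### If infection and vaccination history enter the key secondary (ABCD) model as two main effects, it cannot fit a response deficit specific to sub-population D, and the GMT-ratio interval is somewhat conservative

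*Protocol*

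**What the plan says.** Protocol 11.4.1 defines the primary GMT model in the immunized population (A, B and C). It is a linear model for the 4-week neutralizing activity with administration arm, log10 baseline value and the two histories: "infection and vaccination with SARS-CoV-2 vaccine as covariates". The same section lets the covariates change with enrolment. Protocol 11.4.2.1 carries this model to the wider population: "The same analysis as the primary efficacy analysis will be performed for the PPS for Immunogenicity". Neither section says whether the histories enter as main effects only, as an interaction, or as one combined factor.

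Protocol 11.1 defines the four cells: A (both histories), B (infection only), C (vaccination only) and D (neither). Protocol 5.1.2 uses the two histories as separate randomisation strata, ending with "the presence or absence of a history of vaccination with SARS-CoV-2 vaccine (yes, no) as stratification factors".

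Protocol 3.2 describes people with at least one history as those "in whom a single dose is expected to induce sufficient immunity". It brings D into the key secondary analysis to represent people without basic immunity.

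**The concern.** With three cells, an intercept and two yes/no terms reproduce every cell mean. With four cells they do not: two main effects force A - B - C + D to zero, apart from what baseline titre explains. The protocol's premise is that either exposure prepares a subject for a single dose and that having neither does not. That pattern is an interaction, with A, B and C alike and D lower. A covariate set that is complete for ABC is therefore one term short in the only population that contains D.

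The unfitted part of the D deficit goes into the residual variance. Because arms are randomised 1:1 within history strata, the deficit hardly correlates with treatment. The estimate is unaffected, but its model-based standard error is too large. The stake is precision: the key secondary GMT criterion would be judged on an interval somewhat wider than its nominal level requires.

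**Working it through.** **Inputs from the protocol.** One-sided 2.5% level (11.1: "All hypotheses will be evaluated at a one-sided 2.5% significance level"). GMT-ratio margin 0.67, which is 0.1739 on the log10 scale. Allocation 1:1. SD 0.533 (log10) and 10% non-evaluable (11.6). For ABCD, N = 790 with B = 100 and D = 100, and a true ratio of 1.0.

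**Assumptions.** The 590 subjects in A and C are split 248:342, applying the 42.0% infection share in 11.6 to them. The SD of 0.533 is taken as the within-cell SD. The D deficit g (log10, beyond the additive pattern) is not in the documents, so a range is used.

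**The plan's own figure.** Evaluable per arm: 790 × 0.9 / 2 = 355.5. SE = 0.533 × √(2/355.5) = 0.533 × 0.0750 = 0.0400. Power = Φ(0.1739/0.0400 − 1.96) = 99.2%, against the stated 99.1%, so it reproduces. It takes no stated credit for covariate adjustment.

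**Cost of the missing term.** Leaving out the interaction adds g² / (N × Σ 1/n_cell) to the residual variance. Here Σ 1/n = 1/248 + 1/100 + 1/342 + 1/100 = 0.02696, and 790 × 0.02696 = 21.3, so the added variance is 0.047 g².

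The additive-model SD is √(s² + 0.047 g²). Two values of s are shown: 0.533 (baseline uncorrelated with the 4-week titre) and 0.533 × √(1 − 0.4²) = 0.4885 (assumed within-cell correlation 0.4, with D's baseline equal to the others).

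| Assumed D deficit | g | SD, s = 0.533 | SE inflation | GMT power | SD, s = 0.4885 | SE inflation | GMT power |
|---|---|---|---|---|---|---|---|
| 3-fold | 0.477 | 0.543 | 2% | 99.0% | 0.499 | 2% | 99.6% |
| 10-fold | 1.0 | 0.575 | 8% | 98.1% | 0.534 | 9% | 99.1% |
| 30-fold | 1.477 | 0.622 | 17% | 96.2% | 0.584 | 20% | 97.8% |

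With a four-level factor, power is 99.2% for s = 0.533 and, with SE = 0.4885 × 0.0750 = 0.0366, 99.7% for s = 0.4885.

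**Sensitivity.** If D also has lower baseline titres, the baseline term carries part of the deficit and the inflation is smaller. Across the A:C splits and baseline patterns simulated with D = 100, inflation is about 0-2%, 3-9% and 8-20% for the three deficits. Protocol 11.6 sets no target for D. With s = 0.533 and a tenfold deficit, inflation falls from 8.0% to 6.2% with D = 50 and to 3.6% with D = 20.

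**Validity, by simulation** (4,000 runs per scenario). The estimate is unbiased under both models. Coverage of the 95% interval is 94.9-97.0% for the additive model and 94.8-95.3% with four free cells. At a true ratio of 0.67 the false-pass rate is 1.5-2.2% against 2.3%. Neither exceeds 2.5%.

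**Effect on the decision.** At a tenfold deficit and s = 0.533, the expected lower limit under a true ratio of 1.0 moves from 0.835 to 0.823, far above 0.67. Joint power, computed as the protocol does, moves from 99.1% × 91.2% = 90.4% to 98.1% × 91.2% = 89.5%.

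**The case against.** The strongest reply is that the protocol never says additive. Sub-populations A to D are defined in 11.1, so coding the two histories as four cells is compatible with 11.4.1. Section 11.1 leaves detail to an SAP that is fixed before unblinding, and 11.4.1 lets the covariates change. This stands as a limit on certainty: two main effects are the natural reading, matching two separate strata, but only a reading. It does not dispose of the point. The text names the covariates and extends them unchanged to ABCD, and the permission to change them is tied to enrolment rather than to the four-cell structure, which is known now.

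A second reply is that the documents give no titre for D. That is correct. Section 1.2 cites an observational study with a single-dose vaccine effect of 18.8% without prior infection against about 80% with it. That supports the direction of the gap but measures effectiveness, so it does not supply g.

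A third is that nothing is invalid and little is lost. This also stands. The error is conservative, the primary ABC model is unaffected, and the key secondary also needs seroresponse, whose stated power of 91.2% is the weaker component.

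A reader might infer that GMT power must drop below the stated 99.1%. The documents do not support that. The 99.1% rests on an SD of 0.533 without stated credit for adjustment, whereas the model adjusts for baseline titre. With a correlation of 0.4 and D = 100, power stays at about 99.1% or higher up to a tenfold deficit even under the additive form.

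**Conclusion.** The point holds as a modest loss of precision, conditional on the two histories entering as main effects. In ABCD that form cannot represent a deficit specific to D, so the GMT-ratio estimate remains unbiased while its model-based interval is somewhat conservative. With D = 100, the inflation is about 0-2%, 3-9% and 8-20% for assumed 3-, 10- and 30-fold deficits, and less with fewer D subjects or if baseline titre absorbs the gap. Power falls below 99.1% only if baseline titre explains little or the deficit is very large.

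It would be wrong to infer that the key secondary analysis is biased, or that it risks a false non-inferiority claim: the misfit makes the criterion harder to meet. The balance argument also needs one qualification. Randomisation strata use the rapid-kit antibody result (5.1.2) and the analysis cells use the central-laboratory result (11.1), so balance within cells is close rather than exact. Randomisation still protects the estimate.

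**What to change.** In 11.4.2.1 or in the SAP, before unblinding, state that the ABCD model contains administration arm, log10 baseline titre and one four-level sub-population factor (A, B, C, D). Adding the infection-by-vaccination interaction to the two main effects is equivalent. Leave the primary ABC model as it is, since two terms already fit its three cells.

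The cost is one phrase and one degree of freedom, with no new data, because the trial already classifies every subject into these groups. If D enrols very few subjects the gain shrinks, but the change does no harm. Fixing the form now also narrows the discretion to alter covariates later.

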### 11.4.2.2 Additional Secondary Efficacy Analysis

The incidence of COVID-19 (number of cases per 1000 person-years) for 4 weeks, 12 weeks, and 26 weeks after study drug administration will be calculated. The cumulative incidence will be calculated by administration arm using the Kaplan-Meier method.

The ratios of incidence (DS-5670d group vs. Comirnaty RTU IM group) and their 2-sided 95% confidence intervals will be calculated.

## 11.4.3 Exploratory Efficacy Analysis

Subgroup analyses will be performed for immunogenicity (eg, GMT of blood neutralizing activity against SARS-CoV-2 [Omicron strain XBB.1.5.6], seroresponse rate, etc.) according to baseline characteristics (eg, sex, history of SARS-CoV-2 infection, vaccination with SARS-CoV-2 vaccine).

The GMTs of blood neutralizing activity against SARS-CoV-2 (Omicron strain XBB.1.5.6) at 8 weeks, 12 weeks, 16 weeks, 20 weeks, and 26 weeks after study drug administration and their 2-sided 95% confidence intervals and the seroresponse rates will be calculated.

The GMTs of blood neutralizing activity against SARS-CoV-2\* at 4 weeks, 8 weeks, 12 weeks, 16 weeks, 20 weeks, and 26 weeks after study drug administration and their 2-sided 95% confidence intervals, and the seroresponse rates will be calculated.

\*: Details of variants to be evaluated are specified in a separately prepared plan.

#### 11.4.4 Pharmacokinetic/Pharmacodynamic Analysis

Not applicable.

#### 11.4.5 Safety Analysis

Solicited AEs will be analyzed in the solicited safety analysis set, and other safety analyses will be performed in the safety analysis set. The analyses will be performed based on the study drug that was actually administered to each subject.

##### 11.4.5.1 Analysis of Adverse Events

A treatment-emergent adverse event (TEAE) is defined as any AE that emerges up to 28 days after study drug administration and is not observed before study drug administration but occurs or worsens in severity after study drug administration.

AEs recorded on the AE page of the eCRF will be coded using the International Council for Harmonisation of Technical Requirements for Pharmaceuticals for Human Use (ICH) Medical Dictionary for Regulatory Activities (MedDRA).

##### 11.4.5.1.1 Analysis of Solicited Adverse Events (Collected from the Electronic Diary)

The number and proportion of subjects with solicited AEs (injection site and systemic) that are reported within 7 days after study drug administration will be calculated by event and by administration arm. In addition, solicited AEs will be summarized according to their severity.

A listing for solicited AEs, including the severity, will be prepared for each subject.

In addition, summary statistics of the number of days from study drug administration to the onset of the AE and the duration of symptoms continued in days will be calculated.

For solicited systemic AEs (fever) within 7 days after study drug administration, summary statistics of the highest body temperature will be calculated. Subgroup analyses will be performed on the frequency of solicited AEs according to baseline characteristics (eg, sex, history of SARS-CoV-2 infection, vaccination with SARS-CoV-2 vaccine).

##### 11.4.5.1.2 Analysis of Unsolicited Adverse Events

The number and proportion of subjects with unsolicited TEAEs that are reported within 28 days after study drug administration will be calculated by system organ class (SOC), by preferred term (PT), and by administration arm. In addition, unsolicited TEAEs will be summarized according to their severity and causality with the study drug. Similarly, the number and proportion of subjects with TEAEs leading to permanent discontinuation of study treatment or withdrawal from the study will be summarized in a table. Adverse reactions will be tabulated in a similar manner.

Confidential

A listing for unsolicited AEs (including TEAEs), including the verbatim term, PT, SOC, severity, and causality with the study drug, will be prepared for each subject. Any other required data should be included in the listing.

Subgroup analyses will be performed on the frequency of unsolicited AEs according to baseline characteristics (eg, sex, history of SARS-CoV-2 infection, vaccination with SARS-CoV-2 vaccine). Similar subgroup analyses will also be performed for adverse reactions.

#### 11.4.5.1.3 Analysis of Serious and Other Significant Adverse Events

A table on the number and proportion of subjects with serious TEAEs will be prepared. In the second analyses (analysis for data up to 26 weeks after study drug administration), analysis will be performed in the same way by replacing TEAEs with AEs.

Death, other SAEs, and other significant AEs (including those that led to permanent discontinuation of study treatment or withdrawal from the study) will be listed.

